### Anticipated dates of trial commencement and completion

The study started in January 2023 and is scheduled to be completed in January 2024.

### Sample size calculation

The sample size calculation was based on an alpha (α) level of 0.01, a power (β) of 0.85, and a large effect size, Cohen’s d, of 1.86 for a two-tailed independent t-test. This effect size was calculated based on the results reported by Rocha et al. (2015),
^
18
^ specifically from the mean (SD) values of the control and experimental groups following six manual therapy intervention sessions. Furthermore, the calculation accounted for an anticipated attrition rate of approximately 15%, foreseeing the potential for participant dropout or exclusion. This comprehensive approach to sample size calculation ensures the robustness and reliability of the study’s findings, enabling a precise detection of the large effect size with high statistical confidence. This resulted in a total sample size of 24 people (12 per group) considering a withdrawal rate of 15%.
^
75
^

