**Data collection methods**

Data regarding the outcomes pre and post-intervention will be meticulously collected from the main researcher. The collected information will undergo a thorough examination to analyze the outcomes. Throughout the study, the professor of chest physiotherapy (supervisor) will closely oversee the main researcher administering the study’s data. To ensure the patient adheres to the study, timely messages will be sent to their mobile phones, providing information and reminders regarding upcoming sessions. A 10% drop-out rate has been considered in the sample size calculation, thus minimizing potential interference with the study results.

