### Statistical analysis

The investigation will employ IBM SPSS software, specifically version 28, as the primary analytical tool for comprehensive data processing. Descriptive statistics will be employed to elucidate the distributional characteristics of the dataset. Subsequently, the Shapiro-Wilk test will be utilized to assess data normality for each dependent variable (including US, CWE, ACT, NQ, SF-12v2, and Borg scale) independently. Should normality assumptions be met, parametric tests, specifically the 2×3 ANOVA repeated measures, will be employed, accompanied by Bonferroni adjustment, to investigate the interaction between intervention (experimental and control groups) and time points (0, 6, and 12 weeks). Moreover, to evaluate the homogeneity of variance, Levene’s test will be conducted. The predetermined level of statistical significance is set at p<0.05.

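### The trial is sized at two-sided alpha 0.01 but significance is set at p<0.05, unexplained and with no defined Bonferroni family for the two primary outcomes

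*Protocol article*

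**What the plan says.** All references are to the protocol article.

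- **Sample size calculation.** "The sample size calculation was based on an alpha (α) level of 0.01, a power (β) of 0.85". The effect size is "Cohen’s d, of 1.86 for a two-tailed independent t-test", derived from a cited trial of the same technique in COPD. Attrition is put at about 15%. The result: "This resulted in a total sample size of 24 people (12 per group) considering a withdrawal rate of 15" (per cent).
- **Statistical analysis.** If normality holds, each outcome is analysed by a 2×3 repeated-measures ANOVA for the group-by-time interaction. The same sentence mentions a Bonferroni adjustment but does not say which tests it covers. The section then states: "The predetermined level of statistical significance is set at p<0.05".
- **Abstract and Outcome measures.** There are two primary outcomes, diaphragm excursion and chest expansion.
- **Data collection methods.** "A 10% drop-out rate has been considered in the sample size calculation".

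No section says that 0.01 is a multiplicity-adjusted level, that 0.05 is meant only for secondary outcomes, or that the Bonferroni adjustment takes 0.05 to 0.01.

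**The concern.** The alpha in a sample size justification is normally the alpha at which the primary hypothesis will be tested. Here the two differ by a factor of five on their face. A primary p-value between 0.01 and 0.05 would be significant under the analysis section, yet would miss the level on which the trial's size and its claim to high statistical confidence rest.

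With two primary outcomes, the per-outcome level also determines the chance of a false positive finding. If the level is not settled in advance, it can be chosen with the p-values in view.

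The two drop-out figures describe the same calculation and cannot both be the one used.

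**Working it through.** **Inputs (Sample size calculation).** Two-sided independent t-test, d = 1.86, power 0.85, 1:1 allocation, attrition 15%. The alternative attrition of 10% is from Data collection methods. The alternative alpha of 0.05 is from Statistical analysis. The 0.025 is 0.05/2, the level if Bonferroni spans the two primaries.

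**Formulas.** With n evaluable per arm, power is the probability that a noncentral t variable with 2n − 2 degrees of freedom and noncentrality d·√(n/2) exceeds the two-sided critical value in absolute size. Randomised per arm = n/(1 − attrition), rounded up.

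**Step 1: reproduce the plan's figure (alpha 0.01).**
- n = 9: noncentrality 1.86·√4.5 = 3.95, power 0.830, too low.
- n = 10: noncentrality 1.86·√5 = 4.16, power 0.883, sufficient.
- 10/0.85 = 11.8, so 12 per arm and 24 in total. This matches the article.
- The normal approximation gives 8 per arm, 10 after attrition and 20 in total, so the match comes from the exact t-test.

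**Step 2: the same inputs at other levels.**

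| Two-sided alpha | Evaluable per arm | Power at that n | After 15% loss, per arm | Total |
|---|---|---|---|---|
| 0.01 | 10 | 0.883 | 11.8 → 12 | 24 |
| 0.025 | 8 | 0.872 | 9.4 → 10 | 20 |
| 0.05 | 7 | 0.891 | 8.2 → 9 | 18 |

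Of these levels only 0.01 gives 24, so it was used in the calculation and is not a typing error.

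**Step 3: power of the planned trial for d = 1.86.**

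| Two-sided alpha | 10 evaluable per arm | 12 evaluable per arm |
|---|---|---|
| 0.01 | 0.883 | 0.948 |
| 0.025 | 0.947 | 0.980 |
| 0.05 | 0.975 | 0.992 |

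**Step 4: how far the thresholds lie apart.** The smallest observed standardised difference that is significant in a two-group t-test is t(1 − alpha/2; 2n − 2)·√(2/n). With 12 per arm it is 0.85 at 0.05, 0.98 at 0.025 and 1.15 at 0.01.

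**Step 5: false positives across the two primaries.** For two independent tests, each at level a, the chance of at least one is 1 − (1 − a)².
- a = 0.05: 1 − 0.95² = 0.0975
- a = 0.025: 1 − 0.975² = 0.0494
- a = 0.01: 1 − 0.99² = 0.0199

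Ratios to the sizing level: 0.05/0.01 = 5 and 0.025/0.01 = 2.5. Bonferroni would bring 0.05 down to 0.01 only for a family of 0.05/0.01 = 5 tests, which the article does not state.

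**Step 6: drop-out.** 10/0.85 = 11.8 and 10/0.90 = 11.1. Both round up to 12 per arm.

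**The case against.** **Two rival success criteria?** A reader might infer that the plan sets two decision rules for the same result. It does not. Only the analysis section calls its level predetermined; the sample size section says what the calculation rested on and does not make 0.01 a rule for declaring success. Sizing at a stricter alpha than the test level is conservative and logically possible. This stands. What remains is an unexplained mismatch.

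**Will success be claimed on a criterion five times looser?** A reader might infer this too, and take 9.8% as the trial's error rate. The article does not establish either, because the Bonferroni adjustment may cover the two primaries. The wording ties it to the ANOVA, so coverage cannot be assumed or ruled out. Both figures are conditional. A separate statistical analysis plan could define the family, but the mismatch would remain at 0.025.

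**Is the trial underpowered?** No. On the article's own inputs, testing at 0.05 or 0.025 gives more power than planned, and 0.05 is a conventional level.

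**Must the answer be 0.01?** No. The article does not show which level was intended for the test. A stated 0.05 with a defined family would resolve the matter equally well.

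**Conclusion.** The mismatch is real and concerns the threshold for the primary outcomes. The trial was sized at two-sided 0.01, significance is set at 0.05, and no reason is given. The per-outcome level is therefore nominally 5 times looser than the sizing level (about 9.8% chance of at least one false primary) if Bonferroni does not span the primaries, and 2.5 times looser (about 4.9%) if it does. Planned power is not lost under either reading.

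The error rates assume independent tests; positive correlation between the two outcomes would lower them. The power figures assume d = 1.86 for the outcome tested and a two-group t-test. The planned analysis is a group-by-time interaction over three time points, whose power is not computed here because the article gives no correlation between repeated measurements.

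The 10% and 15% drop-out figures also conflict. This is a point of consistency only: N does not change, and the rounded result cannot show which rate was used.

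**What to change.** Before any unblinded analysis, state one alpha per primary outcome, the same in Sample size calculation and Statistical analysis. Either option works:

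1. **Test as sized.** State that each primary outcome is tested at two-sided 0.01, the level used for the sample size, and that secondary outcomes are reported with confidence intervals and nominal p-values. The cost is a stricter threshold: with 12 per arm, the observed standardised difference needed rises from 0.85 to 1.15.
2. **Keep 0.05 overall.** State that Bonferroni is applied across the two primary outcomes, 0.025 each. Restate the sample size section to give the power of the planned 24 at that level: 0.95 with 10 evaluable per arm for d = 1.86 by the t-test. The cost is a rewritten justification.

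In either case, give one drop-out rate in Sample size calculation and Data collection methods.

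Neither option needs more patients, but the change is more than editorial. The article says the trial began in January 2023 and that protocol modifications are disclosed to the Ethics Committee, and it also says that no further modification is possible. The choice should therefore be dated, documented and reported to the committee as made without sight of unblinded results.

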**Data collection methods**

Data regarding the outcomes pre and post-intervention will be meticulously collected from the main researcher. The collected information will undergo a thorough examination to analyze the outcomes. Throughout the study, the professor of chest physiotherapy (supervisor) will closely oversee the main researcher administering the study’s data. To ensure the patient adheres to the study, timely messages will be sent to their mobile phones, providing information and reminders regarding upcoming sessions. A 10% drop-out rate has been considered in the sample size calculation, thus minimizing potential interference with the study results.

**Data management**

Evaluation data will be sourced from a predefined spreadsheet containing baseline characteristics. A secure database will be employed to store all research-related data securely. Paper copies of evaluation forms signed informed consent forms, and other non-electronic documents will be securely stored in the study environment. A comprehensive backup of the data entries will be generated once a month until the conclusion of the trial.

Upon completion of the study, the Excel spreadsheet will be published and forwarded to the statistician for the necessary analysis. A checklist will help prevent data loss from inefficient staff procedures. Given the extensive follow-up assessment for this experiment, participant retention and completion of follow-up assessments will be notably high. After six weeks from the end of interventions, the participants will be invited to a follow-up examination (12 weeks from the beginning of the trial).

### Statistical analysis

The investigation will employ IBM SPSS software, specifically version 28, as the primary analytical tool for comprehensive data processing. Descriptive statistics will be employed to elucidate the distributional characteristics of the dataset. Subsequently, the Shapiro-Wilk test will be utilized to assess data normality for each dependent variable (including US, CWE, ACT, NQ, SF-12v2, and Borg scale) independently. Should normality assumptions be met, parametric tests, specifically the 2×3 ANOVA repeated measures, will be employed, accompanied by Bonferroni adjustment, to investigate the interaction between intervention (experimental and control groups) and time points (0, 6, and 12 weeks). Moreover, to evaluate the homogeneity of variance, Levene’s test will be conducted. The predetermined level of statistical significance is set at p<0.05.

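### The trial is sized on a single-time-point t-test at alpha 0.01 but analysed by a 2×3 group-by-time interaction at 0.05 with baseline as an outcome, so the stated 85% power does not describe the planned test

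*Protocol article*

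**What the plan says.** The Sample size calculation section of the protocol article is "based on an alpha (α) level of 0.01", with "a power (β) of 0.85" and "a large effect size, Cohen’s d, of 1.86", "for a two-tailed independent t-test". The effect size comes from control and experimental means and SDs in a cited COPD study, taken at one point after six sessions. With 15% attrition this gives 24 people, 12 per group.

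The Statistical analysis section plans something else. Shapiro-Wilk is applied to each dependent variable. Then, "Should normality assumptions be met, parametric tests" are used, namely a 2×3 repeated-measures ANOVA with Bonferroni adjustment, "to investigate the interaction between intervention (experimental and control groups) and time points (0, 6, and 12 weeks"). "The predetermined level of statistical significance is set at p<0.05". Baseline appears only as a level of time.

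The Outcome measures section names two primary outcomes, diaphragm excursion and chest expansion, and no primary time point.

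**The concern.** A power statement holds only for the test, alpha and effect it was computed for. Here both the test and the alpha change between two sections of one article.

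The sizing test asks whether the groups differ at one time after treatment. The interaction test has 2 degrees of freedom and asks whether the group difference varies in any way over three visits, one of which precedes treatment. It spends a degree of freedom on patterns nobody has hypothesised. It also treats the pre-treatment value as an outcome, when that value could be used to reduce noise. In a trial of 24 people this costs precision that could be kept for nothing.

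The normality gate adds a second weakness. The parametric analysis is conditional on a preliminary test with little power at this size, and the article does not say what follows if the test fails.

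**Working it through.** **Inputs from the article.** d = 1.86; alpha 0.01 (sizing) and 0.05 (analysis); power 0.85; 12 per group; 15% attrition; visits at weeks 0, 6 and 12.

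**Assumptions.** 10 evaluable per arm (12 × 0.85 = 10.2); equal variances and equal correlation ρ between visits; the full effect of 1.86 present at week 6. The article gives no ρ, so a range is shown.

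**1. The plan's own figure.** For a two-sided t-test with n per group, the noncentrality is d√(n/2) on 2n − 2 degrees of freedom. At alpha 0.01, n = 9 gives power 0.830. With n = 10 the noncentrality is 1.86 × √5 = 4.16 and power is 0.883. So 10 evaluable per group are needed, and 10/0.85 = 11.8 rounds up to 12 per group, 24 in all. The stated N reproduces. At alpha 0.05 the same t-test with n = 10 has power 0.975.

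**2. Power of the planned interaction.** Let δ be the standardised group difference at each visit. The noncentrality is λ = (n/2) × Σ(δ − mean δ)² / (1 − ρ), referred to F with 2 and 2(2n − 2) = 36 degrees of freedom.

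- Effect persists, δ = (0, 1.86, 1.86): mean 1.24, sum of squares 1.5376 + 0.3844 + 0.3844 = 2.3064, λ = 11.53/(1 − ρ).
- Effect fully lost by week 12, δ = (0, 1.86, 0): mean 0.62, sum of squares again 2.3064, so the same λ and power.
- Effect halves, δ = (0, 1.86, 0.93): mean 0.93, sum of squares 0.8649 + 0.8649 = 1.7298, λ = 8.65/(1 − ρ).

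**3. Comparator.** Week-6 ANCOVA on the baseline value, 2n − 3 = 17 degrees of freedom, by simulation. The closed form with d/√(1 − ρ²) is slightly optimistic because it ignores chance baseline imbalance (0.911 against 0.89 at ρ = 0.3, alpha 0.01).

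| Alpha | ρ | Interaction, persists or fully lost | Interaction, halves | Week-6 ANCOVA |
|---|---|---|---|---|
| 0.05 | 0 | 0.84 | 0.72 | 0.97 |
| 0.05 | 0.1 | 0.88 | 0.76 | 0.97 |
| 0.05 | 0.3 | 0.95 | 0.86 | 0.98 |
| 0.05 | 0.5 | 0.99 | 0.96 | 0.99 |
| 0.01 | 0.1 | 0.68 | 0.52 | 0.86 |
| 0.01 | 0.3 | 0.82 | 0.66 | 0.89 |
| 0.01 | 0.5 | 0.95 | 0.84 | 0.95 |

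If the Bonferroni adjustment were meant to split alpha over the two primary outcomes (0.025 each), the interaction gives 0.75, 0.90 and 0.98 at ρ = 0, 0.3 and 0.5 if the effect persists, and 0.60, 0.79 and 0.92 if it halves.

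**4. A smaller effect.** As an illustration only, take d = 1.2 with all 12 per arm, ρ = 0.3, alpha 0.05 and an effect that halves. The sum of squares is 0.36 + 0.36 = 0.72 and λ = 6 × 0.72/0.7 = 6.17. Interaction power is 0.57, against 0.82 for week-6 ANCOVA.

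**5. The normality gate.** The article does not say how many Shapiro-Wilk tests are run per outcome. With truly normal data and a 0.05 threshold, simulated failure rates are roughly 5% to 11% for one pooled test, 13% to 16% for three visit-level tests, and 24% to 26% for six arm-by-visit tests if any one failure counts.

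**The case against.** The strongest reply is that the plan relaxes alpha from 0.01 to 0.05, and that this largely offsets the change of test. That stands. At d = 1.86 and alpha 0.05, interaction power is below 85% only near ρ = 0 if the effect persists, and up to somewhere between ρ = 0.2 and 0.3 if it halves. At ρ = 0.5 with a persistent effect, 0.989 even exceeds the 0.975 of the unadjusted t-test. A group-by-time ANOVA is also a valid test in a randomised trial.

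Several stronger readings are tempting, and the article does not support them:

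- **That incomplete cases are dropped.** A reader might infer this from how repeated-measures ANOVA software usually behaves. The article does not say so, and a missing-data rule may stand in the full plan.
- **That the analysis is simply unadjusted, or yields no treatment-effect estimate.** A Bonferroni adjustment is planned. Its scope is unclear, but it ordinarily accompanies pairwise comparisons, which give mean differences. What is absent is adjustment for baseline.
- **That a fading effect is always penalised.** Only partial fading is; complete loss by week 12 costs no more than persistence.
- **That the normality gate fails in a quarter of trials.** That is the upper end of a range and depends on a reading the article does not give.

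An alternative analysis after a failed normality test may also be set out in a document not shown. The point here is against the gate itself, which the article does fix.

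**Conclusion.** The mismatch holds on the article's own words: test, alpha and role of baseline differ between sizing and analysis, so the 85% cannot be quoted for the planned test. The N of 24 is correct from its own inputs.

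A reader might conclude that the trial is underpowered for d = 1.86. The figures do not show that at the plan's alpha of 0.05, except at low between-visit correlation. What they show is an avoidable loss of efficiency. It is modest at d = 1.86, larger at alpha 0.01 or under a Bonferroni split, and substantial if the true effect is well below a value borrowed from COPD. These sizes rest on assumed correlations, compound symmetry, 10 completers per arm and a full effect at week 6. That the interaction is the primary test is itself an inference, since the article names no other between-group test and no primary time point. The change is advisable; the trial is not invalid without it.

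**What to change.** - For each primary outcome, replace the interaction test with a baseline-adjusted model. This can be ANCOVA, or a mixed model on weeks 6 and 12 with baseline value, arm, visit and arm-by-visit, using small-sample degrees of freedom.
- Name one post-treatment between-group contrast as primary and report it with a confidence interval. Week 6, the end of treatment, matches the sizing basis best; week 12 then becomes secondary.
- Drop the Shapiro-Wilk gate. Check residuals and give a permutation test of the primary contrast as a sensitivity analysis.
- State one alpha in both sections, say what the Bonferroni adjustment covers, and restate the power for the test actually used, with the assumed correlation.

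The cost is wording: same visits, same data, no added participants. The one statistical downside is that the interaction test is marginally stronger at very high correlation with a fully persistent effect (0.998 against about 0.99 at ρ = 0.7, alpha 0.01).

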**Monitoring**

**
*Data monitoring*
**

A data monitoring committee of members from the UNIWA Physiotherapy Department will periodically review the accumulating data, determining if the trial should be modified or discontinued.

**
*Harms*
**

A clinical staff is going to supervise the entire procedure. Any adverse events will be immediately reported throughout the trial to the Physiotherapy Department of the UNIWA committee.

**
*Auditing*
**

An evaluation of the experiment will be performed each month. Every deviation from the protocol will be recorded and addressed.

**Ethics and dissemination**

**
*Research ethics approval*
**

The Ethics Committee of the UNIWA in Greece approved this study under protocol 90853/04-10-2022. The study follows the Helsinki Declaration’s “Ethical Principles of Medical Research Involving Human Subjects.” Protocol modifications will be disclosed to the Ethics Committee as soon as possible. The trial has been proactively registered in the
ClinicalTrials.gov database with the identification number NCT05709054.

**
*Protocol amendments*
**

The study has already been modified and accepted in accordance with the Ethics Committee of the UNIWA in Greece suggestions. As a result, further modifications could not be made.

**Consent**

Study participants will receive a translated version of the study protocol. Prior to participation, all individuals involved in the study will be fully informed, and written consent will be obtained from each participant.

### Confidentiality

The main researcher will collect personal data during the trial. A confidentiality statement on the permission form will be signed by the main researcher, the subject, and two witnesses. Whenever necessary to disclose information for the study, consent from the patients will always be obtained with utmost assurance of confidentiality.

### Access to data

The main researcher and the statistician will have access to the final trial datasheet.

### Ancillary and post-trial care

The entire procedure will be conducted under the oversight of clinicians and the physiotherapy department of the UNIWA committee. After the trial sessions, the participants will be under supervision for about four weeks so that they can take care if there is any harm.

## Discussion

Although several studies assessing the efficacy of MT in obstructive lung diseases (OLD) have been conducted, drawing definitive conclusions is challenging due to their conflicting results.
^
45
^ A recent systematic review (SR) of the existing literature aimed to identify indications that may underscore the need for differentiated manual therapy (MT) approaches targeting the zone of apposition (ZOA) of the diaphragm in individuals with OLD suffering from pathological adaptations of their chest wall or from respiratory symptoms.
^
76
^ This SR outlined a model illustrating how MT delays the onset of fatigue in respiratory muscles. Additionally, it demonstrated that there is no evidence supporting the effectiveness of MT on the diaphragm for treating individuals (adults) with asthma.
^
76
^ It is noteworthy that two previous studies have examined how MT on the ZOA of the diaphragm hampers the diaphragm’s function and pulmonary function in childhood asthma (RCT)
^
33
^ and in adults with asthma
^
24
^ (pilot study) accordingly. Up to this point, no RCT has comprehensively examined the impact of MDRT, in particular, on the ZOA by MDRT of the diaphragm in adults suffering from asthma.

The primary objective of this RCT is to address the existing literature gap concerning the impact of MDRT on enhancing the functional parameters of individuals with asthma, thereby indicating the need for further research in this domain. Additionally, considering the prevalent pathological changes in the diaphragm muscle among individuals with asthma, it is crucial to determine which anatomical regions and hands-on therapy techniques are most effective for increasing diaphragm excursion in adults with asthma.

The protocol of this study is designed in accordance with accepted practices concerning randomization, concealed allocation, blinding of examiners, and appropriate sample size calculation. This rigorous approach ensures the reliability and robustness of the study’s findings. What sets this study apart is its original investigation into the mechanism of the MDRT on the ZOA of the diaphragm in individuals living with asthma. Finally, several significant constraints must be considered. The study sample is drawn exclusively from a single hospital, potentially limiting the generalizability of the findings. Additionally, the extended experimental period and the substantial number of sessions may lead to participant dropouts.

